**Table 11 Definitions of Analysis Populations**

### 16.3 Demographic and Other Baseline Characteristics

All demographic characteristics, history of disease, CML baseline characteristics (BCR-ABL ratio,), prior treatment history (TKI treatment duration, type of TKI used, IFN therapy, prior unsuccessful discontinuation attempt), and CML characteristics (Sokal, EURO, EUTOS, and ELTS score at primary CML diagnosis, type of BCR-ABL transcript, cytogenetics at primary CML diagnosis) will be tabulated by treatment group and summary measures will be given for the intention-to-treat (ITT) population.

### 16.4 Efficacy Variables

The primary efficacy endpoint is molecular relapse-free survival (RFS).

Time to relapse is defined as the time from randomization to relapse (loss of MMR = increase of BCR-ABL ratio to  $> 0.1\%$  according to the IS) or to death from any cause. Survivors without relapse will be censored on the last date they were known to be alive.

The secondary efficacy endpoints are:

- Treatment outcome correlation with predefined biomarkers ( $>$  or  $<$  95 CD86+pDC before TKI discontinuation, PD-1L, PD1 expression, PR1-CTL and cytokines in peripheral blood measured at date of randomization and at designated time point thereafter).
- Overall survival is defined as time from randomization to death from any cause. Survivors will be censored on the last date they were known to be alive.
- The QoL assessment in this study is planned to gain information on the QoL of CML patients under stopping conditions. The data will be compared between the treatment groups and to QoL of normal population. Furthermore, results of the CML24 Module should be shared with the EORTC group to complete the validation of this questionnaire.

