## 16 Statistical Considerations

### 16.1 Hypotheses

Four hypotheses are tested in hierarchical order. To avoid inflation of type 1 error (false rejection of a null hypothesis), further confirmatory testing has to be stopped as soon as a null hypothesis could not be rejected. All four hypotheses are tested at significance level 0.05.

At first,

Null hypothesis 1: “The probability of molecular relapse-free survival (RFS) 7 months after randomization / 6 months after stopping TKI is not different between the two arms A and B”

is tested against the

Alternative hypothesis 1: “The probability of molecular RFS 7 months after randomization / 6 months after stopping TKI is different between the two arms A and B”.

In case null hypothesis 1 can be rejected,

Null hypothesis 2: “The probability of molecular RFS 13 months after randomization / 12 months after stopping TKI is not different between the two arms A and B”

is tested against the

Alternative hypothesis 2: “The probability of molecular RFS 13 months after randomization / 12 months after stopping TKI is different between the two arms A and B”.

In case null hypothesis 2 can be rejected,

Null hypothesis 3: “No difference in the molecular RFS probabilities between the two arms A and B at any time”

is tested against the

Alternative hypothesis 3: “Molecular RFS probabilities between the two arms A and B are different”.

In case null hypothesis 3 can be rejected,

Null hypothesis 4: “The probability of molecular RFS 25 months after randomization / 24 months after stopping TKI is not different between the two arms A and B”

is tested against the

Alternative hypothesis 4: “The probability of molecular RFS 25 months after randomization / 24 months after stopping TKI is different between the two arms A and B”.

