### Primary efficacy endpoint

The four hypotheses will be tested in hierarchical order, see above. Null hypotheses 1, 2 and 4 will be tested with the two-sided, uncorrected chi-square test. Null hypothesis 3 will be tested with the two-sided log-rank test. The result of BCR-ABL ratio according to the IS needs to be observed. In case of null hypotheses 1, 2, and 4, the BCR-ABL ratio according to the IS has to be available. For the times 6, 12, and 24 months after stop of TKI (i.e. 7, 13, and 25 months after randomization), a time interval around the corresponding time is allowed. Each result should be relatable to exactly one of the visits scheduled in the protocol. Accordingly, intervals are defined by the time in the middle between two visits (schedule of visits see e.g. study flow chart). As visits are scheduled 6, 7, and 8 months after randomization, the interval for relating a result to the 7-month visit is given by 6.5 to 7.5 months after randomization. With visits planned 11, 13, and 15 months, the interval for relating a result to the 13-month visit is given by 12 to 14 months, and finally, with visits foreseen 24, 25, and 36 months after randomization, the result should be recorded within the interval from 24.5 to 30.5 months after randomization. In case of more than one observation within an interval, the approach of Pffirmann et al. will be chosen in order to determine the decisive result. In case of the observation of an extremely unfavourable result prior to the upper time limit of an interval, this result will be carried forward and will be rated as “no MMR/relapse”. Extremely unfavourable results are accelerated disease, blast crisis, or death from any cause. Details on the outcome will be reported. For analyzing null hypothesis 3, it is important to ensure that the BCR-ABL ratio is evaluated at all times foreseen in Table 1. Accelerated disease and blast crisis imply a prior loss of MMR. Molecular RFS probabilities over time will be described by Kaplan-Meier estimates. RFS probabilities over time will be compared by the log-rank test.

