Allogeneic stem cell transplantation in chronic phase or restart of TKI after prior stopping of TKI and without prior loss of MMR will be rated as a drop-out in case this happened prior to an evaluation which would be needed to determine the result for an interval corresponding to hypothesis 1, 2, or 4. In case of hypothesis 3, the observation time of a patient is censored at the time of allogeneic stem cell transplantation or of a restart of TKI without a prior loss of MMR. In this case, the censoring means a loss of information reducing the precision of the estimated probabilities of molecular relapse-free survival but should not alter the estimated probabilities themselves. Accordingly, it is important that the reasons for the reintroduction be clearly stated in any case. Estimated with the Kaplan-Meier method, the probabilities of molecular relapse-free survival describe what to expect, what can be really achieved, if the possibility of a premature TKI restart would not exist.

In case the event “restart of TKI without a prior loss of MMR” has to be regarded as informative with respect to the probabilities of molecular relapse-free survival, the Kaplan-Meier method is not

appropriate. Instead, the cumulative probabilities of a molecular relapse over time have to be estimated by the cumulative incidence function (CIF) 60. The event “restart of TKI without a prior loss of MMR” is then regarded as a competing risk.

Whatever the situation, non-informative or informative censoring, the cumulative incidence function will be calculated (in addition). It will present the cumulative probabilities of a molecular relapse under consideration of the presence of the competing event “restart of TKI without a prior loss of MMR” and also provide an estimation of the probabilities of this competing event itself.

Differences between the treatment strategies prior to discontinuation will be tested by the Gray test (Gray RJ et al., Ann Stat, 1988), if the assumption of non-informative censoring does not hold.

As explorative analyses, depending on the endpoint, multivariate logistic or Cox regression analyses will be performed to analyse the influence of baseline covariates such as the effect of different duration of prior TKI therapy.

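### Molecular RFS is censored at the last date known alive rather than at the last BCR-ABL PCR, which biases the time-to-event RFS analyses upward

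*Protocol*

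**What the plan says.** Section 16.4 counts two events for RFS: loss of MMR, meaning a BCR-ABL ratio above 0.1% on the international scale, and death. For patients with neither, it says "Survivors without relapse will be censored on the last date they were known to be alive". A few lines later the same rule is given for overall survival: "Survivors will be censored on the last date they were known to be alive".

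Section 16.7 (primary efficacy endpoint) handles the data differently by hypothesis:

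- **Fixed-time tests:** "In case of null hypotheses 1, 2, and 4, the BCR-ABL ratio according to the IS has to be available". The result must fall in a window around month 7, 13 or 25.
- **H3, test:** "Null hypothesis 3 will be tested with the two-sided log-rank test".
- **H3, completeness of PCR:** "For analyzing null hypothesis 3, it is important to ensure that the BCR-ABL ratio is evaluated at all times foreseen in Table 1". No rule follows for a patient in whom this fails.
- **H3, censoring:** "the observation time of a patient is censored at the time of allogeneic stem cell transplantation or of a restart of TKI" where there was no prior loss of MMR.

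Section 16.9 analyses molecular RFS again as a time-to-event variable at the end of the post-study follow-up.

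**The concern.** The censoring date should be the last date on which the event could have been seen. For overall survival that is the last date known alive. For molecular relapse it is the last PCR. Under section 16.4 as worded, a patient whose last PCR was at month 3 but who is known alive at month 25 contributes 22 months of relapse-free time during which no relapse could be detected. Section 8.2.4 says that most patients who relapse do so within 6 months off TKI, so monitoring that stops early misses the period of highest risk.

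The result is a Kaplan-Meier curve that is too high, by an amount that grows with the share of patients who stop PCR. If the share differs between arms, the comparison is distorted in favour of the arm with more loss. If it is equal, the difference between arms shrinks.

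The exception for transplantation and TKI restart stands only in section 16.7. Section 16.4 does not refer to it, so for such a patient the two sections, each taken alone, give different censoring dates.

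**Working it through.** **Inputs from the protocol (16.1, 16.10).** RFS in arm B of 55%, 50% and 45% at months 7, 13 and 25; 20 points more in arm A; 10% drop-out; 214 randomized, so 107 per arm; hazard ratio 1.8603 for the log-rank test; and "All four hypotheses are tested at significance level 0.05".

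**The plan's own figures.**
- The chi-square formula without continuity correction for 45% against 65% gives 96 per arm, or 192; 192/0.9 = 213.3, rounded up to 214.
- Log-rank: expected events 96 × (0.55 + 0.35) = 86.4. By Schoenfeld, √(86.4/4) × ln(1.8603) − 1.96 = 4.648 × 0.6207 − 1.96 = 0.925, a power of 82%. The plan says slightly above 80%.

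These figures reproduce, and the censoring rule does not enter them.

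**Bias with equal loss (assumed).** Suppose a share d stops PCR, uniformly over months 1 to 7, and stays known alive to month 25. Take no relapse before TKI stop at month 1 and a constant hazard from month 1 to 7. The last PCR is then at month 1, 2, 3, 4, 5 or 6 with equal probability. The chance that no relapse had been seen by then is the mean of S^(k/6) for k = 0 to 5, where S is RFS at month 7:

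- Arm B, S = 0.55: (1 + 0.905 + 0.819 + 0.742 + 0.671 + 0.608)/6 = 0.791
- Arm A, S = 0.75: (1 + 0.953 + 0.909 + 0.866 + 0.825 + 0.787)/6 = 0.890

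Under the last-alive rule nobody is censored before month 25, so Kaplan-Meier RFS equals the share without an observed relapse, (1 − d) × true RFS + d × that mean. With d = 10%:

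| Arm | Calculation | Reads | True |
|---|---|---|---|
| A | 0.9 × 0.65 + 0.1 × 0.890 | 67.4% | 65% |
| B | 0.9 × 0.45 + 0.1 × 0.791 | 48.4% | 45% |

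The difference becomes 19.0 points instead of 20. Simulation with relapse detected at the scheduled visits gives the same values, and censoring at the last PCR returns about 65% and 45%.

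**Sensitivity to timing, by simulation.** With 10% loss all before month 6, RFS reads 67.6% and 49.0%, and log-rank power with 214 randomized falls from 0.859 to 0.839. With loss spread over months 1 to 25 it reads 65.8% and 46.2%.

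**Unequal loss, no true effect (assumed).** With 15% lost in arm A and 5% in arm B over months 1 to 7:
- Arm A: 0.85 × 0.45 + 0.15 × 0.791 = 50.1%
- Arm B: 0.95 × 0.45 + 0.05 × 0.791 = 46.7%
- Spurious gap: 3.4 points

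Simulated two-sided log-rank error, taken alone, was 6.7% to 8.0% over several runs with 107 per arm, against about 5% when censoring at the last PCR. With 20% against 5% it was about 10 to 11%.

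**The same scenarios inside the hierarchy.** H3's null, no difference at any time, implies the nulls of H1 and H2. A false H3 claim therefore needs false rejections of H1 and H2 first, and those tests do not use the censoring rule. H1, H2 and H3 were all rejected in only about 1 to 2% of runs.

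**The case against.** The strongest reply is that few patients would be affected:

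- **PCR continues after treatment stops.** The legend to Tables 1 and 2 and section 12.1.4 require BCR-ABL follow-up every three months to month 25 after a premature end of treatment. Stopping AOP2014 is not stopping PCR.
- **Withdrawal is largely covered.** Section 13.1 has patients who withdraw consent resume TKI, and section 16.7 then censors them for H3 at the restart.
- **The two dates often coincide.** PCR is scheduled at every visit, and section 12.1.7 collects survival and PCR together at months 36, 48 and 60.

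All of this stands and limits the size. What remains is patients who stop PCR without a documented TKI restart and are still known alive. Section 16.7 does not cover them, and section 16.4 keeps them at risk.

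Four stronger readings are tempting, and the protocol does not support them:

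- **That the primary result is biased.** The month-7 test, like H2 and H4, uses PCR results in visit windows.
- **That the trial's false-positive rate rises.** The 7 to 8% belongs to a log-rank test standing alone, which is not how H3 is tested.
- **That arm A is favoured.** Intolerance of interferon makes more loss there conceivable, but the protocol gives only a 10% drop-out overall. Equal loss narrows the difference.
- **That 16.4 and 16.7 flatly contradict each other.** Section 16.7 reads naturally as a specific H3 rule within a general definition. The fault is that 16.4 does not refer to it.

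One might also compute (0.65 × 96 + 11)/107 = 69% and (0.45 × 96 + 11)/107 = 51%. That supposes every lost patient left before any could relapse, so it is a ceiling.

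**Conclusion.** The point holds for time-to-event RFS only: the H3 log-rank test, the Kaplan-Meier curves, the Cox models on RFS, and the post-study time-to-event analysis. The censoring rule suits overall survival and does not suit an event that only a PCR can show. At the assumed 10% loss per arm over months 1 to 7, the overstatement at month 25 is about 2.4 points in arm A and 3.4 in arm B; it is about 1 point in each arm if loss is spread over months 1 to 25. Unequal loss of 15% against 5% with no true effect gives a gap of about 3 points. All loss rates, and the premise that these patients stay known alive to month 25, are assumptions.

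The consequence is a distorted H3 p-value and distorted estimates, in a direction that depends on which arm loses more PCR follow-up. H3 also decides whether H4 is tested, so its p-value should rest on a sound definition.

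**What to change.** In section 16.4, replace the RFS censoring sentence by: for molecular RFS, patients without relapse or death are censored at the date of their last evaluable BCR-ABL (IS) PCR, or at allogeneic transplantation or TKI restart without prior loss of MMR, if that is earlier. Use identical wording in sections 16.7 and 16.9, and keep the last-known-alive date for overall survival only.

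The cost is wording. PCR dates are already collected, and the sample size and planned power do not change.

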### 16.5 Quality of life assessment

Primary objective:

- determine prospectively QoL of patients after stopping +/- IFN from randomization until EOS. This is a secondary endpoint and therefore mandatory.

Secondary objectives:

- to evaluate the impact of treatment discontinuation of QoL according to treatment arm
- to evaluate the impact of IFN therapy on QoL and to validate the CML24 module

The aim of QoL evaluation in this study is to get a better understanding of the effects of the treatment in terms of frequency and degree of related side effects from the perspective of the patients.

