| TKI intake for 30 days                                                                                                            |                                   | X                   |                                                                     |   |   |   |   |   |   |   |     |    |    |    |                           |                    |    |    |    |    |      |    |    |            |   |                                      |
| AOP2014 dosing (biweekly, 50
µg for the first 4 weeks , from
month 2 full dose of 100 µg )
and accounting |                                   | 50 µg        | 100 µg                                                       |   |   |   |   |   |   |   |     |    |    |    |                           |                    |    |    |    |    |      |    |    |            |   |                                      |
|                                                                                                                                   |                                   | X                   | X                                                                   | X | X | X | X | X | X | X | X   | X  | X  | X  |                           |                    |    |    |    |    |      |    |    |            |   |                                      |
| Local tolerability assessment                                                                                                     |                                   | X                   | X                                                                   | X | X | X | X | X | X | X | X   | X  | X  | X  |                           |                    |    |    |    |    |      |    |    |            |   |                                      |
| Quality of life                                                                                                                   |                                   | X                   | X                                                                   | X | X | X | X | X | X | X | X   | X  | X  | X  |                           |                    |    |    |    |    |      |    |    |            |   |                                      |

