### 4.2 Secondary endpoints

- RFS 13 months after randomization
- RFS 25 months after randomization
- Safety, tolerability and toxicity based on incidences of adverse events, serious adverse events, frequency of clinical laboratory tests by worst toxicity grade
- Quality of life (EORTC QLQ-C30 and EORTC-QLQ-CML24 questionnaires) The QoL assessment in this study is planned to gain information on the QoL of CML patients under stopping conditions. The data will be compared between the treatment groups and to QoL of normal population. Furthermore, results of the CML24 module should be shared with the EORTC group to complete the validation of this questionnaire
- Explore the value of  $95 \text{ CD86+ pDC} / 10^5$  lymphocytes at baseline (before TKI stop) as a predictor of TFR
- Overall survival (OS), defined as the time between the date of randomization and the date of death from any cause.
- Explore immunological and genetic biomarkers to study biology of TFR, and identify predictors IFN response (e.g. mRNA sequencing of whole blood or leukocyte subpopulations, PD-L1-, PD1-, CD62L- measurements by FACS on peripheral blood subsets, T-cell activation and exhaustion marker measurements, PR1-CTL assessment and cytokines).
- Evaluation of cytokines/chemokines (i.e., IL-6, IFN- $\alpha$ , IL 10, and others).
- Kinetics of BCR-ABL transcript level over time after TKI stop

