#### 8.2.4 AOP2014 treatment duration

The optimal duration of IFN therapy to maintain deep molecular remission induced by TKI induction therapy is unknown. In a small uncontrolled study, 6 months of IFN maintenance after TKI discontinuation were ineffective in sustaining TFR^43. On the other hand, an IFN maintenance duration of more than 4 years may not be needed. In CML, high avidity anti-leukemic T-cell clones are depleted at de novo diagnosis, but can be re-shaped in remission after longer therapy. For example, IFN treatment of at least two to three years restored the skewed T-cell receptor repertoire in hairy cell leukemia and stimulated expansion of specific, high avidity anti-leukemic T-cell clones in complete cytogenetic responders. Since IFN-induced cytogenetic remissions emerge significantly more slowly than with imatinib (in median more than 12 months after commencing treatment) the minimum effective IFN maintenance treatment duration is estimated to be probably between 1 and 2 years.

Patients in arm A are therefore treated with AOP2014 for 15 months and then observed for an additional 10 months without any therapy. Since most patients relapse within 6 months off any TKI (only 7% of all relapses occurred after months +9 after TKI discontinuation in the A-STIM trial), the evaluation of RFS 25 months after randomization (last visit) will enable an objective judgment about the efficacy of AOP2014 in preventing relapses after TKI discontinuation.

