#### **12.1.6 Surveillance phase (month 15 to month 25)**

In **arm A** surveillance phase refers to the time between month +15 to +25 (see study flow chart 1.1 and Table 1 and Table 2).

CAVE: the scheduled follow up differs slightly in arm A compared to arm B in that additional BCR-ABL RT-PCR (IS) assessments are required 16, 17, 19, 20, and 22.5 months after randomization (see study flow chart 1.1 and Table 1 and Table 2).

For patients randomized into **arm B**, surveillance phase refers to the entire time between month 0 to 25, because these patients never receive any study specific medication.

Patients, who relapse during surveillance phase **in arm A or arm B**, will resume TKI therapy and again perform an EOT visit; see 12.1.5. The molecular BCR-ABL RT-PCR (IS) follow up will then be performed and documented in the e-CRF (every 3 months after resuming the TKI until month 25 (see study flow chart 1.1 and Table 1 and Table 2).

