### 12.2.16 Quality of Life Questionnaires

QoL will be assessed with the EORTC Quality of Life Questionnaire (QLQ-C30) version 3, the CML24 module.

QoL questionnaires must be filled out at the hospital/practice when the patient comes for a scheduled visit. The questionnaires will be handed out to the patients by the investigator or a study nurse prior to seeing the doctor for clinical evaluations. Patients will be asked to fill out the questionnaires as completely and accurately as possible. The average time to complete the entire questionnaire is approximately 10-15 minutes. QoL should be assessed at time-points indicated in 12.1 and Table 1 and Table 2.

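### As read, Table 1 ends arm A quality-of-life assessment at month 15 while Table 2 adds month 25 for arm B, so no planned QoL visit covers arm A's drug-free phase

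*Protocol*

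**What the plan says.** Section 16.5 states the main QoL aim as "determine prospectively QoL of patients after stopping +/- IFN from randomization until EOS. This is a secondary endpoint and therefore mandatory". A further aim there is "to evaluate the impact of treatment discontinuation of QoL according to treatment arm". Section 4.2 adds that "The data will be compared between the treatment groups and to QoL of normal population". Section 12.2.16 leaves the timing to the schedules: "QoL should be assessed at time-points indicated in 12.1 and Table 1 and Table 2".

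Within section 12.1, QoL is listed for the baseline visit (12.1.2) and for visits 2 to 12 (12.1.3). Section 12.1.4 refers month 15 to the tables. Section 12.1.6, on the surveillance phase, does not mention QoL. The "Quality of life" rows of Tables 1 and 2 therefore decide what is collected after month 15.

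On the course of arm A, section 8.2.4 says: "Patients in arm A are therefore treated with AOP2014 for 15 months and then observed for an additional 10 months without any therapy". Section 12.1.6 agrees that in arm A the "surveillance phase refers to the time between month +15 to +25". The only difference between the arms that it declares for this period is that in arm A "additional BCR-ABL RT-PCR (IS) assessments are required 16, 17, 19, 20, and 22.5 months after randomization".

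**The concern.** QoL is a mandatory secondary endpoint, to be followed to the end of study and compared by arm. If the tables are followed as read, arm B is measured at month 25 and arm A is not. The text gives no reason for the difference.

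The missing period matters for the trial's own argument. Section 2.4 rests the rationale on temporary AOP2014 maintenance that leads to treatment-free remission, and presents that remission as the outcome of greatest value to patients. Arm A can reach it as planned only after month 15. Section 10.2 lists influenza-like illness, fatigue, joint pain and depression among the events related to AOP2014. Whether patients report relief once the drug stops is thus part of the benefit claim, and the schedule provides no planned measurement of it. Questionnaires that were not completed at the time cannot be recovered later.

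**Working it through.** No sample-size or power figure is involved. The check reads the QoL row of each table against its row of months.

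| | Arm A (Table 1) | Arm B (Table 2) |
|---|---|---|
| Months 0, 1, 2, 3, 4, 5, 6, 7, 8, 9.5, 11, 13, 15 | 13 marks | 13 marks |
| After month 15, before month 25 | none | none |
| Month 25 | none | 1 mark |
| Total | 13 | 14 |

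1. **Matched time points.** There are 13, of which 13 − 1 = 12 come after baseline. The unmatched time point is month 25, in arm B only.

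2. **Arm A's drug-free phase.** It runs for 25 − 15 = 10 months. Table 1 has nine visits in it (months 16, 17, 18, 19, 20, 21, 22.5, 24 and 25). QoL is marked at 0 of 9.

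3. **Could a column shift explain the gap?** Some Table 1 rows, such as ECOG and BCR-ABL, sit one column out after month 15. A shift would move a mark but not remove it, and every QoL cell after month 15 is empty. Physical examination, ECOG, BCR-ABL and concomitant treatment all carry marks in the surveillance columns.

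4. **Could a single mark have been lost?** This cannot be excluded. The FACS and IFN-prediction-score rows show the same pattern: month 25 is marked in Table 2 and not in Table 1. Yet sections 12.2.11 and 19.3 plan translational sampling at months 18 and 25 without limiting it to one arm. Either Table 1 itself omits month-25 items, or isolated marks were lost in conversion from the PDF. Neither table marks month 18 for those two rows, so the tables also differ from the text at a visit where the two arms look alike.

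5. **What does EOS mean?** Section 12.1.8 gives 25 months per patient and defines the end of the study as last patient last visit with database closure. Sections 14.2 and 14.5 place it at month 15 when setting the period for AE and SAE recording. If EOS is month 25, arm A's QoL row falls short. If EOS is month 15, arm B's month-25 mark goes beyond the objective. On either reading one table disagrees with section 16.5.

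6. **After the repair.** Adding month 25 to Table 1 gives 14 assessments in each arm, all matched. Arm A then has one planned assessment in its drug-free phase instead of none.

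**The case against.** The strongest objection is that the gap may not exist in the source document. Table 1 is damaged on its right-hand side, and three rows lack the month-25 mark that Table 2 carries. That dense rows survived does not prove that an isolated mark did. This stands, and it is why the first step is to look at the source table.

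A second objection is that the protocol itself twice equates end of study with month 15, and that section 16.5 describes the aim of QoL evaluation in terms of treatment side effects. A month-15 window is then a possible reading. It does not settle the matter, because arm B's month-25 assessment would become the unexplained entry.

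Stronger readings are tempting and are not supported:

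- A reader might infer that the QoL objective cannot be answered. Thirteen matched assessments address the stated aims at least in part, and on-drug against off-drug is the right contrast for the impact of interferon on QoL. No stated aim names recovery after AOP2014 stops.
- A reader might infer that every arm A questionnaire after baseline is completed on interferon. That describes the schedule only. Under section 13.1, patients who stop treatment early at their own request and consent to follow-up continue their visits. Patients who relapse in surveillance have a further EOT visit, which might yield a questionnaire. Neither group represents planned drug-free remission.
- A reader might count the affected patients from the assumed 65% and 45% RFS at month 25. With 107 randomized per arm this gives 0.65 × 107 ≈ 70 and 0.45 × 107 ≈ 48. With the 96 evaluable per arm in section 16.10 it gives 0.65 × 96 ≈ 62 and 0.45 × 96 ≈ 43. These are scenario figures for a subset selected by outcome. A comparison restricted to relapse-free patients would not be a randomized one.

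QoL also lies outside the four confirmatory hypotheses, and section 16.7 analyses secondary endpoints descriptively. That limits the weight of the point without removing it.

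**Conclusion.** The point holds in a limited form. As read, the two schedules disagree on one assessment: 13 planned QoL time points in arm A against 14 in arm B, with month 25 unmatched and none of arm A's nine surveillance visits covered. The comparison through month 15 is unaffected. What is missing is any planned QoL measurement in arm A's 10 drug-free months, and with it the only scheduled off-AOP2014 comparison between the arms.

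This rests on two assumptions: that the empty cells in Table 1 reflect the source document, and that EOS for QoL means the 25 months given per patient. If the source table carries a month-25 mark, the scheduling gap disappears and only the wording on end of study needs tidying. If EOS was meant as month 15, the tables still have to be reconciled. Confidence is moderate. The primary endpoint is not touched, but a mandatory secondary endpoint is, and the repair is nearly free, so the sponsor should make it.

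**What to change.** 1. Check the month-25 column of the QoL row in the source Table 1, and the FACS and IFN-score rows at the same time.
2. If the QoL mark is absent, add QLQ-C30 and CML24 at arm A's month-25 visit to match Table 2.
3. State in section 16.5 that EOS for QoL means month 25, so that it is not confused with the month-15 limit in sections 14.2 and 14.5.
4. Report the month-25 comparison separately from the on-treatment comparison through month 15. Include all patients with data, in the arm to which they were randomized, and give the number contributing in each arm.

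The cost is a schedule-table amendment and one questionnaire of 10 to 15 minutes (section 12.2.16) at a visit that Table 1 already contains with a BCR-ABL test. Further questionnaires at months 18 and 21 would be optional and are not needed to resolve this point.
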